**Inclusion criteria**
Aged ≥18 years.Have a sufficient command of the Dutch language.Diagnosed according to the criteria of the Diagnostic and Statistical Manual of Mental Disorders, Fifth Edition, as having schizophrenia, schizophreniform disorder, schizoaffective disorder, another specified schizophrenia spectrum disorder, other psychotic disorder, unspecified schizophrenia spectrum disorder, or other psychotic disorder.Was defined as treatment resistant. In our study, we will determine treatment resistance for each symptom domain (positive and negative domains) using scores on the Positive and Negative Syndrome Scale (PANSS) [48]. Following the remission criteria proposed by Andreasen et al [49], symptoms must be (1) at least moderately severe, that is, a PANSS score of 5 on at least two items or a PANSS score of 6 on 1 item or (2) mildly severe, that is, a PANSS score of at least 4 on one of the items P1, P2, P3, N1, N4, N6, G5, and G9. Moreover, the patient must show impaired psychosocial functioning, with a score of <60 on the Social and Occupational Functioning Assessment Scale [50]. Concerning medical treatment, there must have been 2 adequate treatment episodes in the past with different antipsychotic drugs. The duration of this antipsychotic treatment needs to have been for at least six weeks at the therapeutic dosage. We will use the minimum maintenance dose from the Dutch Summary of Product Characteristics from the Rules Governing Medicinal Products in the European Union to determine the therapeutic dosage criterion. We will also determine medication adherence using data from the electronic prescription system in patients’ files and reports. This will enable us to see whether medication is still being held for patients at a pharmacy that they have not yet picked up.

Inclusion criteria for informal caregivers.
**Inclusion criteria**
The informal caregiver is assigned by the patient.The informal caregiver is aged ≥18 years.The informal caregiver has a sufficient command of the Dutch language.The informal caregiver is able and willing to give informed consent.

#### Sample Size

To gain insight into the implementation process of the CC-TRS, the factors influencing this implementation and preliminary effects at the patient level, sufficient variation in patient characteristics, caregiver characteristics, and the context of implementation are needed. Within the context of the 2 FACT teams and an EIT, we believe that it will be sufficient to include 20 patients in our study to achieve the desired variation. If patients decide to stop the CC-TRS interventions, they will be asked to remain in the study purely for the purpose of carrying out a follow-up analysis.

#### Modifications Due to the COVID-19 Pandemic

Owing to the COVID-19 pandemic, face-to-face contact with participants is no longer self-evident. Therefore, we will have to make modifications to the treatment and measurements of the study depending on the applicable COVID-19 guidelines at that juncture. All modifications will, of course, be in accordance with the advice and guidelines of the mental health organization where the study will be conducted as well as the National Institute for Public Health and the Environment in the Netherlands.

Treatment-based contact will be face-to-face as much as possible. When face-to-face contact is not possible or the patient feels uncomfortable with face-to-face contact and refuses to do so, video calling will be the preferred form of contact, followed by telephone calling.

Team members will preferably engage in contact through video calling. This also applies to feedback meetings with all team members. Measurements with patients will preferably take place face-to-face. Interviews will be conducted via video calling when face-to-face contact is not possible. We will adhere to the recommendations of Opler [51] for conducting Positive and Negative Syndrome Scale interviews via video calling. These recommendations relate to—among other things—video connectivity, high-bandwidth connections, and the webcam's field of view. Research assistants will also receive additional training on how to conduct interviews via video calling.

Group interviews with caregivers and care professionals will take place 1 year after the start of the first inclusion, which means that it will be conducted in October 2022. If there are still restrictions on face-to-face contact at that juncture, group interviews will be conducted by video calling.

#### Recruitment of Patients

Patients who receive treatment in the participating teams will be screened for eligibility for the study. This screening process will divide participants into 3 categories. First, patients who met the inclusion criteria will be invited to participate in the study. Second, patients who do not meet all the inclusion criteria at the time of screening might be potential participants in the future. Third, patients who meet exclusion criteria are excluded. Every 3 months, we will reassess both the patients within the second group and those who are new to the team.

The care manager will screen selected patients supervised by the quality consultants. Patients who meet the inclusion criteria and agree to contact the principal investigator will receive verbal and written information about the study and CC-TRS intervention. The patient will have at least 7 days to consider participation. In the case of consent to participate, the principal investigator will determine the patient’s decisional capacity using the Brief Assessment of Capacity to Consent, over telephone. The patients will be then asked to sign an informed consent form. The reasons for refusal to participate will be registered. The patients will sign an informed consent form before they are included in the study. At T0, we will determine whether a patient is eligible for inclusion in the study.

In the informed consent procedure, patients will be asked to point out an informal caregiver. The informal caregivers will also receive verbal and written information about the study and CC-TRS from the principal investigator. After at least 7 days to consider participation, informal caregivers will be asked for consent for participation in the study. In the case of a positive response, the informal caregiver will sign an informed consent form.

As part of the informed consent procedure, patients will be asked to name an informal caregiver, who will subsequently be asked to give their consent to participate in the study.

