### Data Collection

#### Patients

We will perform document analysis 3 (T3), 6 (T6), 9 (T9), and 12 (T12) months after a patient is included in the study. As part of these document analyses, we will conduct an intervention check to ascertain whether the CC-TRS is being carried out in adherence to the intervention protocol. Therefore, it will be possible to quantify the care received by patients. As part of the intervention, both patients and informal caregivers will discuss their experiences with the CC-TRS as part of their treatment plan evaluations with the CC team. This will be reported in patient files, thus offering the opportunity to gain insight into their experiences with the CC-TRS by conducting document analysis. We expect the CC-TRS to produce positive effects on somatic outcomes such as metabolic syndrome, cardiovascular risks, and (risk of) diabetes mellitus. Therefore, the following somatic outcomes of patients will be extracted from their medical files at baseline (T0) and after 12 months (T12): height, weight, BMI, waist circumference, systolic and diastolic blood pressure, lipid profile, and fasting blood glucose levels. Moreover, the presence of cardiovascular disease, diabetes mellitus, or hypertension will be registered, including the use of medications for these disorders.

There will be 3 face-to-face measurements: when patients are included in the study (T0), after 6 months (T6), and after 12 months (T12). The questionnaires used for quantitative data collection at T0, T6, and T12 are summarized in Table 1. The questionnaires *Consumer Quality Index* and *Experiences with CC-TRS* will only be administered at T12. At T12, after completion of all quantitative measurements, a 60-minute interview will be conducted with the patients. In this interview, a topic list will be used to discuss the results of the quantitative data, the course of the treatment, the implementation of the various treatment components, and the experiences of patients with the CC-TRS. Furthermore, patients will be asked which factors and specific aspects of the CC-TRS influenced the outcomes and whether the desired effects were achieved. All the interviews will be audiotaped and transcribed verbatim.

Patients will receive €7.50 (US $8.02) for each of the first 3 face-to-face measurements and €15 (US $16.04) for the fourth face-to-face measurement in the form of gift vouchers. In addition, their travel expenses will be reimbursed.

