MANSA^g^	This is a 16-item questionnaire that measures the quality of life, with a particular focus on satisfaction with life as a whole and with different life domains [63]. In addition to the MANSA, we will also ask patients to give a score between 0 and 10 to describe their quality of life in general.	The MANSA is a brief instrument for assessing quality of life focusing on satisfaction with life as a whole and with life domains. Its psychometric properties appear satisfactory (Cronbach α=.74 for the satisfaction rating) [63].
PANSS^h^	This is one of the most widely used instruments for measuring the presence and severity of positive, negative, and general psychopathological symptoms of schizophrenia. The PANSS is a 30-item structured interview [48].	The PANSS has good interrater reliability, adequate construct validity, high internal reliability, appropriate test-retest reliability, and external validity [48,64-66].
SDM-Q-9^i^	This is a self-report instrument comprising 9 items that was developed to measure patients’ perceptions of the shared decision-making process (SDM-Q-9) [67].	The SDM-Q-9 has a good acceptance, internal consistency, and acceptable to good convergent validity (Cronbach α=.88) [67].
SOFAS^j^	This is a 1-item rating (0-100) that assesses social and occupational functioning (independently of the severity of psychological symptoms) [50].	To our knowledge, the SOFAS has not yet been tested for psychometric quality. We will use this questionnaire to assess the criteria for treatment-resistant schizophrenia as established by the Working Group of the Treatment Response and Resistance in Psychosis. They use SOFAS to operationalize functional limitations [68].
Questionnaire experiences with treatment	This is a self-developed questionnaire containing 11 items about satisfaction with treatment in general and 4 items about satisfaction with treatment via the Collaborative Care program for patients with treatment-resistant schizophrenia.	The questionnaire has not been examined for psychometric quality.

^a^CGI: Clinical Global Impression.

^b^CQi: Consumer Quality Index (Geestelijke Gezondheidszorg en Verslavingszorg Ambulant).

^c^DES: Dutch Empowerment Scale.

^d^MHRM: Mental Health Recovery Measure.

^e^PIH: Partners in Health scale.

^f^HoNOS: Health of the Nation Outcome Scale.

^g^MANSA: Manchester Short Assessment of Quality of Life.

^h^PANSS: Positive and Negative Syndrome Scale.

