In the cross-case analyses, the findings from the 20 single-case analyses will be analyzed at the group level. In 3 ways, we will investigate the extent to which the implementation plans were successfully carried out. First, we will conduct an intervention check through document analysis. In this way, we systematically identify if and to what extent the interventions have been implemented. Second, we will discuss, through feedback meetings with team members, which components of the CC-TRS are implemented as planned and which components are not, whether all preconditions are met sufficiently, and discuss the teams’ needs to overcome experienced barriers regarding implementation. Feedback meetings will be audiotaped and summarized, with notable quotes being transcribed verbatim. Third, in supervision meetings, CNS and CC nurses will discuss their own considerations and explanations for the extent and manner in which interventions are implemented at the patient level. Noteworthy findings and considerations will be noted. We will quantitatively analyze the overall effects of CC-TRS on different outcome measures. To this end, exploratory analyses will be performed on patients (n=20) using the Friedman Test (nonparametric variant of the repeated measures analysis of variance). Next, we will descriptively analyze the quantitative data related to patients’ satisfaction with the CC-TRS program, by using the *Consumer Quality Index* and the questionnaire *Experiences with CC-TRS*. Following this, an overall analysis of individual interviews with patients will be conducted. Descriptive qualitative analyses will then be performed to explore the experiences of patients in the CC-TRS intervention program. Subsequently, the data from informal caregivers will be analyzed, first quantitatively (FPCR and the questionnaire *Evaluation informal caregivers CC-TRS*), followed by a qualitative descriptive analysis of the data generated in the focus group interviews. The next step will be to analyze the data pertaining to care professionals. The first quantitative analysis will be conducted on caregivers’ satisfaction with the training program. This will be followed by a qualitative analysis of the data generated through feedback meetings. Finally, data from the caregivers’ interviews will be descriptively analyzed. Through recourse to the method of content analysis [70], patient records will be analyzed to investigate the implementation of the CC-TRS.

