Several other issues were carefully considered in this study. First, we consider the inclusion strategy of participants. In clinical practice, and also noticed by other researchers [73], besides the Diagnostic and Statistical Manual of Mental Disorders diagnoses of schizophrenia or schizoaffective disorder, other schizophrenia spectrum disorders are also diagnosed in cases of persistent psychotic symptoms. To avoid the risk of excluding patients who meet the criteria for TRS, we will include a broader range of Diagnostic and Statistical Manual of Mental Disorders diagnoses. At T0, we will determine whether a patient is eligible for inclusion in the study. The second consideration is the exclusion of inpatient treatment settings. We expect the CC-TRS to be important in inpatient long-term care units given the presence of (undertreated) patients with TRS in such units. However, for practical reasons and to limit the scope of our study, we now focus exclusively on outpatient settings. To determine the effectiveness of the intervention in both outpatient and inpatient treatment settings unambiguously, it is desirable to conduct an experimental study on the effects of the intervention. If our study shows that the CC-TRS has positive effects on the outpatient population, future research should determine whether these effects can also be achieved in the inpatient population.

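### SOFAS and PANSS scores that decide entry at T0 are also the baseline of the uncontrolled analysis, so part of any gain may be regression to the mean

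*Protocol article*

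**What the plan says.** **Entry.** Under Inclusion criteria, treatment resistance requires symptoms above a PANSS item threshold and impaired functioning, "with a score of <60 on the Social and Occupational Functioning Assessment Scale". Several PANSS routes qualify. The lowest bar is "a PANSS score of at least 4 on one of the items P1, P2, P3, N1, N4, N6, G5, and G9". Two adequate past antipsychotic episodes are also required.

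**Timing.** Under Recruitment of Patients the care manager screens first, and consent follows. Then: "At T0, we will determine whether a patient is eligible for inclusion in the study". The sentence is repeated under Strengths and Limitations.

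**Baseline.** Data Collection (Patients) places the face-to-face measurements at T0, T6 and T12. Table 1 lists PANSS and SOFAS among them and says of SOFAS: "We will use this questionnaire to assess the criteria for treatment-resistant schizophrenia". No second rating before treatment is described.

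**Analysis.** Under Analyses: "We will quantitatively analyze the overall effects of CC-TRS on different outcome measures". The method is an exploratory Friedman test in the 20 patients. There is no comparison group.

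**Use of the result.** Strengths and Limitations first calls an experimental study desirable for settling effectiveness in outpatients and inpatients. The next sentence names inpatients as the group to study next, and it begins: "If our study shows that the CC-TRS has positive effects on the outpatient population, future research should determine whether these effects". The listed limitations mention neither regression to the mean nor the missing comparison group.

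**The concern.** One rating does two jobs. A patient whose T0 SOFAS is low partly through rating error or a passing bad spell qualifies, and a patient with the opposite error does not. Among those who enter, the average T0 error is therefore unfavourable. It is not repeated at T6 and T12, so mean scores improve even if nobody's underlying state changes. Without a comparison group the analysis cannot separate this from the programme.

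Psychosocial functioning and symptoms are the first two outcomes named in the preliminary-effects question, and they are the two measured by the entry scales. The quantitative results also feed the T12 interviews with patients and care professionals, where outcomes are to be explained. An artefact could be given a qualitative explanation there.

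**Working it through.** **The plan's own figure.** The sample size of 20 is justified by variation between cases. No significance level, power, effect size or SD is stated, so there is nothing to reproduce.

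**Inputs from the article:** SOFAS cut-off 60; n = 20; three visits; Friedman test; eligibility decided at T0.

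**Assumed inputs (not in the article):** SOFAS mean in the screened population 45-60; SD 10-12; retest correlation r 0.6-0.9 for step 1 and 0.6 or 0.8 for step 2; 5% level; normal scores; deviations independent between visits.

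**Step 1: expected SOFAS gain with no true change.** With c = (60 − mean)/SD,

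gain = (1 − r) × SD × φ(c)/Φ(c).

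- Low end (mean 45, SD 10, r 0.9): c = 1.5; φ/Φ = 0.1295/0.9332 = 0.139; gain = 0.1 × 10 × 0.139 = 0.14 points.
- High end (mean 60, SD 12, r 0.6): c = 0; φ/Φ = 0.3989/0.5 = 0.798; gain = 0.4 × 12 × 0.798 = 3.83 points.
- Ranges by mean, over SD 10-12 and r 0.9-0.6: 0.14-0.98 (mean 45), 0.29-1.70 (50), 0.51-2.65 (55), 0.80-3.83 (60).

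**Step 2: how often the Friedman test rejects with no true change.** Simulation, n = 20, 4,000 replicates per cell. The pre-screen columns also require a separate earlier rating on the same scale, with the same r, to fall below the cut-off.

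| Cut-off relative to screened mean | Share qualifying on one rating | T0 only, r 0.8 | T0 only, r 0.6 | Pre-screen and T0, r 0.8 | Pre-screen and T0, r 0.6 |
|---|---|---|---|---|---|
| 1.5 SD above | 93% | 5.3% | 5.5% | 5.4% | 5.2% |
| 1 SD above | 84% | 6.2% | 7.6% | 5.9% | 6.2% |
| 0.5 SD above | 69% | 8.8% | 14.4% | 7.1% | 9.7% |
| At the mean | 50% | 15.4% | 30.1% | 9.0% | 16.3% |

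The simulation standard error near 5% is √(0.05 × 0.95/4000) = 0.34 percentage points, so the top row cannot be told apart from 5%.

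**Step 3: is the double use of T0 the cause?** With entry decided on one rating and the baseline taken from a new one, mean change was 0.00 SD and rejection 4.8-5.8% in every scenario tried. In this model the inflation comes from the double use alone.

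**PANSS.** No figure was computed, because that would need item-level distributions. One item scored 4 or more among eight can be enough, which is a low bar in persistently ill patients, and one item's error is a small part of a 30-item scale. A smaller effect than for SOFAS is likely.

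**The case against.** **The aims are modest.** Effects are called preliminary, the analysis exploratory, and quantitative generalisation is disclaimed under Objectives. No significance level or decision rule is stated, so the 5% error rate is this review's yardstick. This limits the consequences. It does not remove a bias inside the 20 patients, and the text does not name that bias.

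**Selection at T0 may be weak.** The care manager has already screened patients against the criteria, and these teams treat severe mental illness, so few may fail the SOFAS cut-off at T0. This stands: a low screened mean takes the inflation close to nothing. Whether the pre-screen uses formal ratings is not stated.

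A reader might infer three stronger points that the article does not support:

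- *That repeated screening adds to the bias.* The text says "Every 3 months, we will reassess both the patients within the second group and those who are new to the team", but this concerns patients sorted at screening. It does not say that T0 ratings are repeated until someone qualifies, and a patient may become eligible on other grounds, such as completing a second antipsychotic episode.
- *That the reported improvement will be an artefact.* Only the direction of the bias is known.
- *That the authors overlook controlled evidence.* The sentence before the conditional one already calls an experimental study desirable, outpatients included. The fault is that the two sentences do not fit together.

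**Conclusion.** The point holds at moderate severity. T0 SOFAS and PANSS serve as both entry test and baseline in an uncontrolled comparison described as an analysis of effects, and the resulting bias runs toward benefit.

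Its size cannot be fixed from the article. Under the assumptions above, the SOFAS gain from selection alone is about 0.1-3.8 points. Null rejection is about 6-8% with the cut-off 1 SD above the screened mean and 15-30% with it at the mean. These fall to about 6% and 9-16% if the pre-screen used the same scale. The upper figures need a screened population in which half the patients would fail the cut-off. PANSS is probably less affected.

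**What to change.** 1. **Analyses.** Describe SOFAS and PANSS results as *change from T0 during CC-TRS*, not as effects. Show the observed change beside the change expected from regression to the mean over a stated range of reliability and population mean. T6-T12 change can be added as a supplementary description. It does not start from the selected baseline, but it misses any early benefit.
2. **Weight of evidence.** Give more weight to self-report scales not used for selection (MANSA, PIH, SDM-Q-9). HoNOS is less suitable, because it also covers symptoms and social functioning and may share T0 rating error.
3. **Limitations.** Name regression to the mean and the lack of a comparison group.
4. **Strengths and Limitations, conditional sentence.** Make it consistent with the sentence before it, so that a favourable outpatient change is not treated as an established effect before a controlled study.

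**Cost.** Wording and a few lines of calculation, with no new visits. SOFAS and PANSS results will look somewhat less favourable. A separate baseline rating after eligibility would remove the problem in the model used here, but it adds a measurement and recruitment has already begun.

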#### Research Assistants

Trained research assistants will perform the measurements required for this study. These assistants will not be involved in either the implementation or execution of the CC-TRS. Interrater reliability will be assessed using a simulated interview.

